### Patient and public involvement statement

Patients were not directly involved in the initial design, recruitment or conduct of this RCT. However, patient representatives will actively be involved in the interpretation of the trial findings. A group of patient advisors, independent of the research team and representative of the target population, will be invited to participate in a results interpretation workshop after data analysis is completed. During this workshop, key findings will be reviewed and discussed from a patient perspective. Their feedback will be incorporated into the framing of the discussion section.

### Statistical approach

Detailed methodology for summaries and statistical analyses of the data collected in this study is documented in a statistical analysis plan, which will be finalised before database closure. The primary analysis population is the full analysis set, which, following intention-to-treat principles, includes all randomised patients. Every effort will be made to minimise the number of patients lost to follow-up. A secondary analysis population, the per-protocol (PP) population, will be prospectively defined to exclude patients with major protocol violations. Specifically, the following criteria will lead to exclusion from the PP population: major violation of study inclusion or study exclusion criteria, treatment not according to randomisation (eg, nutritional protocol not followed in a patient in the intervention group or control group patients receiving structured nutritional therapy) and patients lost to follow-up. A consort diagram will be reported as recommended.

The primary analysis will include only patients enrolled at the Swiss sites, as their recruitment and trial completion are expected to occur earlier due to the earlier trial start. After the Spanish cohort has also completed the study, a secondary publication is planned using a pooled, patient-level analysis.

For the primary endpoint, the time to death due to any cause, we will use a log-rank test to compare survival distributions in the control and intervention groups. To adjust for additional variables, we will fit a Cox proportional hazards model including age, Barthel’s index at baseline, study centre and initial NRS as covariates. For all variables included in the model, we will estimate the effect sizes and report 95% CIs. For the secondary endpoints, we will use survival analysis for all time-to-event outcomes and fit logistic and linear regression models for binary and continuous outcomes, respectively. Moreover, we will assess changes in functional outcomes and quality of life using a linear mixed model approach to account for the repeated measurements per patient. We will report effect estimates and CIs without p value adjustment for multiple comparisons. Additionally, we will analyse win-ratios to compare patient pairs across hierarchical clinical endpoints, determining a ‘win’ or ‘loss’ based on the most clinically important outcome within each pair.

We will perform predefined subgroup analyses by including interaction terms in the regression models to test effect modification by important baseline factors. Specifically, we will look at patient age (<60, 60–75, >75 years), sex, nutritional risk stratified by initial NRS (3, 4, >4 points), BMI (<20, 20–25, >25–30, >30 kg/m^2^), main medical diagnosis at the index hospital stay (systemic infection, heart failure, acute renal failure, gastrointestinal disease, tumour, COPD) and influential comorbidities (diabetes, chronic renal failure, status of inflammation) as well as socio-economic status (including food insecurity).

No interim analyses are planned.

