### Study endpoints

All patients in both groups are contacted every 6 months by structured phone calls from a blinded study nurse or dietitian to assess primary and secondary endpoints until the patient reaches the primary endpoint, drops out or until the study is terminated. If necessary, information on patient mortality, rehospitalisations or major complications during the follow-up period is confirmed through family members or the patient’s primary care physician.

The primary endpoint is defined as the time from trial inclusion to death from any cause (ie, all-cause mortality). Secondary endpoints are defined as:

Time to non-elective hospital readmission after discharge from the index hospital stay.Time to the first major complication including death, bacterial infection with need for antibiotic treatment, major cardiovascular event (ie, stroke, intracranial bleeding, cardiac arrest, myocardial infarction) or pulmonary embolism, acute renal failure, gastro-intestinal events (including haemorrhage, intestinal perforation, acute pancreatitis).Changes in functional status measured by the Barthel’s index (scores range from 0 to 100, with higher scores indicating better functional status).^25^Changes in quality of life measured with the EQ-5D index (German Version, EQ-5D index values range from 0 to 1, with higher scores indicating better quality of life) including the VAS (EQ-5D VAS) (scores range from 0 to 100, with higher scores indicating better health status).

We will follow participants until the end of the study, ie, until approximately 247 mortality events have occurred. We expect a maximum follow-up period of 5 years for patients enrolled at the start of the study. In addition to blinded telephone follow-up examinations, the unblinded study dietitian conducts home visits or in-clinic at 3, 6 and 12 months for all patients to evaluate the study-specific nutritional outcomes.

Body weight.Calf circumference to assess muscle mass.Bioelectrical impedance analysis to assess body composition (fat-free mass, fat mass).Hand grip by means of handgrip strength through dynamometry (Jamar Hydraulic Hand Dynamometer) to assess muscle strength.^26^

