**Figure 3 F3:**
[figure not shown]
Algorithm for nutritional strategy used in EFFORTII. aBW, adjusted body weight; DF, disease factor; GFR, glomerular filtration rate; PAL, physical activity level; REE, resting energy expenditure.

In the control group, the study dietitian provides education on protein-rich and energy-rich diets at hospital discharge, but no additional oral nutritional supplements or nutritional counselling are offered to patients.

The trial includes the following visits:

During hospitalisation: screening of patients, patient’s enrolment.Before hospital discharge: inclusion and randomisation, first visit of study dietitian.Every 2–4 weeks phone: phone call by unblinded study dietitian to monitor and potentially adjust nutritional intervention (intervention group only).At 3, 6 and 12 months: home visit (or in-clinic visits) by unblinded study dietitian to assess nutritional outcomes (both groups).Every 6 months: phone call follow-up for outcome assessment by blinded study nurse (both groups).

Figure 4 shows the overall patient flow of EFFORTII.

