### Sample size considerations

We designed the trial in collaboration with the Department of Clinical Research of University Hospital in Basel as an event-driven trial to show the superiority of continued nutritional therapy for patients discharged from the hospital compared with usual care regarding mortality. The sample size was calculated for the Swiss cohort only. We targeted 247 mortality events and a total sample size of at least 802 participants, who are assigned 1:1 to nutritional therapy and the usual care groups. We hypothesised an incidence of mortality of 20% per year in the usual care group, an effect estimate of 0.7, a type I error rate of 0.05, a power of 80%, a recruitment period of 1.5 years, a trial duration of 3 years and a withdrawal rate of 10% per year of follow-up.

Additionally, we calculated the required sample size for several different assumptions regarding the effect of our intervention, study durations and recruitment periods. Assuming an HR of only 0.75 and a power of 80%, the required sample size would be 1200. Thus, we recruit at least 802 participants but can continue to reach a maximal total of 1200 patients depending on timing/success of recruitment. Figure 5 demonstrates effect size estimations for the number of events needed in the trial.

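### Excluding patients lost to follow-up from the secondary per-protocol set selects on the outcome; for time to death they should be kept and censored (primary analysis unaffected)

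*Protocol article*

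**What the plan says.** The Statistical approach section of the protocol article sets two populations. The first is primary: "The primary analysis population is the full analysis set, which, following intention-to-treat principles, includes all randomised patients". The second is the PP set: "A secondary analysis population, the per-protocol (PP) population, will be prospectively defined to exclude patients with major protocol violations". Three kinds of patient are then removed from the PP set: those with major eligibility violations, those not treated as randomised, and those lost to follow-up. The end of that list reads "control group patients receiving structured nutritional therapy) and patients lost to follow-up". Loss to follow-up is a criterion of its own there, not an example of another one.

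Study endpoints makes the primary endpoint time to death from any cause. For its analysis, Statistical approach states "we will use a log-rank test to compare survival distributions in the control and intervention groups", with a Cox model for adjustment.

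Sample size considerations assumes "a withdrawal rate of 10% per year of follow-up", one rate without distinction by arm. Study endpoints also allows deaths to be confirmed through relatives or the primary care physician.

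**The concern.** A patient lost at month 18 has contributed 18 months alive under observation. Log-rank and Cox methods use that time by censoring at month 18. The PP rule removes the patient altogether. A patient who dies under observation before any loss can never meet the criterion, so the rule takes away follow-up without an observed death and removes no observed death. This distorts the death rate even when loss has nothing to do with prognosis, a situation in which censoring would be unbiased.

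The rule also does not fit its own heading. The PP set is meant to remove major protocol violations, and being lost to follow-up is not in itself a violation.

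At stake is the interpretation of the PP mortality result. Absolute PP mortality would be too high in both arms. If loss differed between arms, a gap between the PP and full-analysis-set hazard ratios could reflect adherence, the deletion rule, or both, and a reader could not separate them.

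**Working it through.** **Inputs (Sample size considerations).** Control mortality 20% per year, hazard ratio 0.70, type I error 0.05, power 80%, recruitment 1.5 years, trial duration 3 years, withdrawal 10% per year.

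**Assumptions added here.** Constant hazards; uniform accrual, so administrative follow-up c is uniform between 1.5 and 3 years; loss independent of death; all withdrawal counted as loss; arm-specific loss rates, which the article does not give.

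**1. The plan's own figures.**
- Events, two-sided: 4 × (1.960 + 0.842)² / (ln 0.70)² = 246.8, so 247. This matches.
- Hazards: control λ = −ln(0.80) = 0.2231; intervention 0.70 × 0.2231 = 0.1562; loss η = −ln(0.90) = 0.1054.
- Probability of an observed death: λ/(λ+η) × (1 − E[exp(−(λ+η)c)]). Control: 0.2231/0.3285 × (1 − 0.4824) = 0.352. Intervention: 0.1562/0.2616 × (1 − 0.5587) = 0.263 (0.2635 unrounded).
- Mean 0.3076; 247/0.3076 = 803, against 802 stated. The model represents the plan adequately.

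**2. Who is deleted at 10% per year in both arms.**
- Probability of loss: η/(λ+η) × (1 − E[exp(−(λ+η)c)]). Control 0.166, intervention 0.178, so about 17% overall.
- Crude control mortality with everyone kept: 35.2%. With lost patients removed: 0.352/(1 − 0.166) = 42.2%.
- Control deaths per person-year (simulation, millions of patients): 0.223 with censoring, about 0.249 to 0.250 with deletion, a rise of about 12%.

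**3. Why the hazard is distorted.** Let q(t) be the probability that a patient still under observation at time t is later lost. After deletion the hazard at t is λ/(1 − q(t)), so the PP hazard ratio at t is HR × (1 − q_control)/(1 − q_intervention).
- Equal loss, HR 0.70, at t = 0: 0.70 × 0.834/0.822 = 0.710. The effect fades as t approaches the end of follow-up, and the overall Cox estimate is 0.70 (0.702 to 0.705 between runs).
- Loss of 15% control and 5% intervention, HR 1.00, at t = 0: (1 − 0.242)/(1 − 0.085) = 0.83. Over the whole of follow-up the Cox estimate is 0.89.

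**4. Cox hazard ratio after deletion (simulation).** Yearly loss rates are assumed, except that 10% is the planned withdrawal rate.

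| Loss, control / intervention | True HR 1.00 | True HR 0.70 |
|---|---|---|
| 10% / 10% | 1.00 | 0.70 |
| 4% / 2% | 0.975 to 0.98 | 0.69 |
| 12% / 8% | 0.95 to 0.96 | 0.67 |
| 10% / 5% | 0.94 to 0.95 | 0.66 |
| 5% / 10% | 1.06 | 0.74 to 0.75 |
| 15% / 5% | 0.89 | 0.62 to 0.63 |
| 5% / 15% | 1.12 | 0.79 to 0.80 |

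Ranges show variation between simulation runs. With lost patients censored instead, the Cox estimate returned the true value in every row within simulation error. That is expected here because loss was simulated as independent of death.

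**The case against.** **The primary result is safe.** A reader might infer that the trial's mortality conclusion or its type I error is at risk. The article does not support that. The primary analysis keeps all randomised patients, and the 247 events and the power do not rest on the PP set. In simulated null trials of 802 patients with 15%/5% loss, the PP test rejected in about 16% to 17%. That is the rejection rate of a secondary analysis under an assumed imbalance, not the trial's error rate. The article gives the PP set no decision role and does not call it a robustness check. This objection stands and limits the severity.

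**Ascertainment is the same in both arms.** A reader might also infer that control patients are followed less closely for death and so will be lost more often. The outcome schedule says otherwise: "All patients in both groups are contacted every 6 months by structured phone calls", and the dietitian visits at 3, 6 and 12 months are for all patients. What differs is treatment contact every 2 to 4 weeks, described as "phone call by unblinded study dietitian to monitor and potentially adjust nutritional intervention (intervention group only", and free supplements. These could retain patients or burden them, so the direction of any difference is unknown. This stands.

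**Withdrawal is not the same as loss.** Deaths may be confirmed through relatives or the physician, so a patient who stops visits need not be lost. The 17% is therefore an upper-end figure. At an assumed 3% true loss per year in each arm, about 5% would be deleted. This stands.

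**A common loss rate leaves the hazard ratio almost unchanged.** True, and one common rate is all the article states. The absolute PP mortality is still inflated.

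**Censoring is not always unbiased.** Also true: in frail patients loss may be related to prognosis, and censoring is then biased as well. That gives deletion no advantage, since it discards the same patients' observed time on top.

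**Conclusion.** The criterion is wrong as written, for a secondary analysis only. It is a rule the article states, so the point does not depend on the analysis plan that is not shown.

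The part that needs no difference between arms is the inflation of absolute PP mortality: control from about 35% to 42% and the control death rate up about 12%, if all planned withdrawal is loss, and less if vital status is recovered for some of those who withdraw. Bias in the PP hazard ratio requires loss to differ by arm. Under the assumed rates it runs from about 2% for a small difference (4%/2%) to about 11% or 12% in either direction for a large one (15%/5% or 5%/15%). The article gives no arm-specific rates, so these are illustrations and not predictions.

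Severity: should be fixed; it does not threaten the primary analysis.

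**What to change.** Delete loss to follow-up from the PP exclusion criteria in the protocol, and carry the same definition into the statistical analysis plan. Keep these patients in the PP set if they meet its other criteria, and censor them at the date last known alive. State that this relies on loss being independent of death. Report the number lost and the timing of loss by arm.

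The cost is one phrase and one table, with no new data. The article says that the analysis plan is finalised before database closure, so the definition can be settled there before results are known.

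This change does not make the PP comparison unbiased. Exclusion for treatment not according to randomisation is also decided after randomisation, and it remains a limitation to state beside any PP result.

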### Data collected at study entry

After trial inclusion, each patient receives a structured systematic medical and nutritional assessment by the study dietitian and study physician including:

Sociodemographics and anthropometrics (eg, age, sex, weight and height for calculation of body mass index (BMI), food insecurity survey).Detailed medical history including information about comorbidities, drug use and results of blood work-up as available from routine care (eg, kidney function based on estimated glomerular filtration rate, electrolytes, albumin, levels of trace elements and vitamins, results of endocrine function).Current nutritional intake regarding protein and energy estimated from the patient’s medical charts (as available) or using a structured 24-hour recall.Baseline nutritional risk based on risk scores (eg, NRS, Mini Nutritional Assessment or similar).Baseline muscle mass (calf circumference).Basal metabolic rate/energy requirements calculated based on the Harris-Benedict equation.Baseline muscle strength (hand grip dynamometry).Baseline body composition (bioelectrical impedance analysis (BIA).Baseline functional status (Barthel Index).Baseline quality of life (European Quality of Life 5 Dimensions (EQ-5D) Index and EQ-5D visual analogue scale (VAS)).

We also systematically collect blood samples at the main site (Cantonal Hospital Aarau) on study enrolment (day 0) for later batch analyses of blood biomarkers (ancillary project).

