### Randomisation

After patient enrolment, a member of the study team randomises patients 1:1 into the intervention or control group at a time point close to hospital discharge according to a pre-specified, computer-generated, web-based randomisation scheme using the centralised secuTrial website. The randomisation is stratified for site and NRS total score.

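### The primary endpoint is tested with a log-rank test, no stratification or adjustment stated, although a more efficient Cox model is already listed: forgone power, not an error

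*Protocol article*

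**What the plan says.** The Randomisation section states: "The randomisation is stratified for site and NRS total score". The endpoint (Study endpoints) is all-cause death: "The primary endpoint is defined as the time from trial inclusion to death from any cause".

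For that endpoint, the section Statistical approach says "we will use a log-rank test to compare survival distributions in the control and intervention groups". It mentions neither stratification nor covariates for this test. The next sentence begins "To adjust for additional variables, we will fit a Cox proportional hazards model including age" and goes on to name the baseline Barthel index, "study centre and initial NRS as covariates". Effect sizes with 95% confidence intervals are promised for all variables in that model.

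Both stratification factors and two likely predictors of death are therefore in a prespecified analysis, but that analysis comes second and is presented as an adjustment. Under Sample size considerations the article says: "We targeted 247 mortality events and a total sample size of at least 802 participants". The stated assumptions are 20% yearly control mortality, an effect of 0.7, type I error 0.05 and 80% power.

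**The concern.** Two mechanisms are in play. First, when randomisation is balanced within prognostic strata and the test ignores them, the variance estimate is somewhat too large and the test somewhat conservative. Second, in survival data a treatment contrast that leaves out strong predictors is pulled towards 1, so a test adjusted for them has more power for the same number of deaths.

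The second mechanism matters more here. Adults of all ages with chronic disease enrol, and the investigators themselves chose age and Barthel for adjustment. The design has no reserve: 247 deaths give 80% at a hazard ratio of 0.70. If the true ratio were 0.75, the article's own alternative, and the trial still stopped at 247 deaths, power would be about 62%. Information already collected at baseline could raise power without further patients or deaths.

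**Working it through.** **1. Reproduce the plan's figure.** The Schoenfeld formula with 1:1 allocation, two-sided alpha 0.05 and 80% power gives d = 4(1.960 + 0.842)² / (ln 0.70)² = 31.40 / 0.1272 = 246.8, so 247 deaths.

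For the sample size, take yearly probabilities of 20% (death, control) and 10% (withdrawal), uniform accrual over 1.5 years and 3 years in total. The mean event probability is then 0.3076, and 247 / 0.3076 = 803, against 802 stated. The plan's figures are those of an unadjusted log-rank test, and they reproduce.

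**2. Power at a hazard ratio of 0.75 with 247 deaths.** (√247 / 2) × |ln 0.75| − 1.960 = 7.858 × 0.2877 − 1.960 = 0.30, and Φ(0.30) = 0.62.

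**3. Simulation.** From the article: 802 patients, 247 deaths, 11 Swiss sites, the Cox covariates. Assumed: three NRS levels, permuted blocks of 4 within site × NRS, and the prognostic strengths below. Age and Barthel enter as one combined score.

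| Setting | SD of age + Barthel log-hazard score | Log HR per NRS step | SD of site effects |
|---|---|---|---|
| None | 0 | 0 | 0 |
| Weak | 0.3 | 0.1 | 0.1 |
| Moderate | 0.6 | 0.2 | 0.2 |
| Strong | 0.9 | 0.3 | 0.3 |
| Strata only | 0 | 0.3 | 0.3 |

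Power with the conditional hazard ratio held at 0.70 (4,000 trials each):

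| Setting | Log-rank | Log-rank stratified by site × NRS | Listed Cox model | Cox minus log-rank |
|---|---|---|---|---|
| None | 80.1% | 78.8% | 80.4% | 0.3 |
| Weak | 79.4% | 77.8% | 80.6% | 1.2 |
| Moderate | 74.5% | 73.7% | 81.1% | 6.6 |
| Strong | 66.0% | 66.2% | 81.1% | 15.1 |
| Strata only | 79.5% | 78.8% | 80.9% | 1.4 |

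Power with the marginal hazard ratio held near 0.70 (simulated mean 0.704 to 0.705; 3,000 trials each):

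| Setting | Conditional HR used | Log-rank | Stratified log-rank | Listed Cox model | Cox minus log-rank |
|---|---|---|---|---|---|
| Weak | 0.697 | 78.9% | 78.1% | 80.5% | 1.6 |
| Moderate | 0.682 | 78.9% | 78.4% | 84.8% | 5.9 |
| Strong | 0.657 | 78.5% | 78.2% | 90.4% | 11.9 |

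**4. Source of the gain.** With prognostic strata and no other predictors, the Cox model gains 1.4 points. Stratifying the log-rank test by site × NRS changes power by −1.6 to +0.2 points over the weak, moderate and strong settings. The rest of the gain comes from age and Barthel.

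**5. Type I error.** For the log-rank test, 12,000 null trials per setting (Monte Carlo standard error 0.002) gave 4.9% (weak), 5.0% (moderate), 4.7% (strong) and 4.5% (strata only). Figures of 3.2 to 3.5% appear only with very strong assumed strata, such as a hazard ratio of 2.0 per NRS level with a site SD of 0.5. For the Cox model, 4,000 null trials per setting gave 4.5 to 5.2%, so its gain is not bought with extra type I error.

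**6. Scale in deaths.** At a hazard ratio of 0.70, 78.9% power needs 4(1.960 + 0.803)² / 0.1272 ≈ 240 deaths, and 84.8% needs 4(1.960 + 1.028)² / 0.1272 ≈ 281. In the moderate setting, adjustment is worth about 40 deaths.

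**The case against.** The strongest reply is that nothing is wrong. The log-rank test matches the sample size calculation. The article gives only an effect estimate of 0.7 and names no covariates. Read as a marginal hazard ratio, 0.70 gives the log-rank test its planned power. This stands. A reader might infer from the first power table that the trial falls short of 80%, but that needs 0.70 to be the conditional ratio, which the article does not say.

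A reader might also infer that ignoring the strata makes the test materially conservative, or that stratifying the log-rank test would repair it. The checks support neither: type I error is 4.5 to 5.0% at the strengths examined, and stratifying alone gains almost nothing.

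The SAP, which is not shown, may qualify the test or say which analysis is confirmatory. That is fair, and silence on such detail is not held against the article. But the article does name the log-rank test for the primary endpoint and gives the Cox model an adjusting role, and that choice can be discussed as stated.

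It is also late. Recruitment began in 2021, and the Swiss sites had 80% of planned patients when Spanish sites joined in 2024. Participants and caregivers are not blinded. The change is therefore acceptable only if made without sight of comparative data. No interim analysis is planned, which helps.

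**Conclusion.** The point holds as forgone efficiency. The stated test is valid and consistent with the design, and the listed Cox model would use the same deaths better. The gain is about 0 to 2 points of power if the predictors are weak, about 6 to 7 if moderate and about 12 to 15 if strong.

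The direction is secure. The size is not, because it rests on prognostic strengths that the article does not give. The simulated model also had the correct form for the age and Barthel score; a poorly fitting form would reduce the gain.

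Main diagnosis, including tumour, is a planned subgroup factor, and a reader might conclude that the model must contain it. Nothing in the article gives its prevalence or its effect on mortality, so adding it is optional and not part of this point.

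**What to change.** In the SAP, before database closure and before any comparative data are seen, name the treatment effect from the already listed Cox model (age, baseline Barthel, NRS, centre) as the single confirmatory test and estimate. Fix a rule for merging small centres, set on blinded data. Keep the log-rank test as a sensitivity analysis. Record the date of the change and that it was made without access to outcomes by arm.

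The cost is a documented change of the lead analysis, with no new data, patients or deaths. The downside is that the reported hazard ratio becomes conditional on the covariates and lies further from 1 than the marginal one (0.68 against 0.70 in the moderate setting). It should be labelled so.

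### The Cox model for mortality omits main diagnosis; adding at least tumour yes/no would be a cheap gain in efficiency for the adjusted hazard ratio

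*Protocol article*

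**What the plan says.** All statements are in the protocol article.

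- **Endpoint** (Study endpoints): "The primary endpoint is defined as the time from trial inclusion to death from any cause".
- **Test** (Statistical approach): "we will use a log-rank test to compare survival distributions in the control and intervention groups".
- **Adjusted model** (same section): the covariate list is introduced with "To adjust for additional variables, we will fit a Cox proportional hazards model including age". Three more covariates follow: the Barthel score on entry, the centre and the NRS. Effect sizes with 95% confidence intervals are to be reported from this model. The log-rank test gives none, and no other effect estimate is named for mortality.
- **Subgroups** (same section): interaction terms will be fitted "to test effect modification by important baseline factors". One of these factors is "main medical diagnosis at the index hospital stay (systemic infection, heart failure, acute renal failure, gastrointestinal disease, tumour, COPD"). A further item on the list reads "influential comorbidities (diabetes, chronic renal failure, status of inflammation").
- **Data** (Data collected at study entry): "Detailed medical history including information about comorbidities" is gathered after inclusion. Blood results are collected only where routine care provides them.
- **Stratification** (Randomisation): site and NRS total score.
- **Timing** (Statistical approach): the SAP is to be finalised before the database closes.

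**The concern.** The enrolled population mixes tumour, heart failure, COPD, infection and gastrointestinal disease. For death from any cause over several years, having a tumour is plausibly one of the stronger predictors. It is balanced neither by the stratification nor by the model, yet the trial must code main diagnosis anyway for its interaction models.

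Leaving a strong predictor out of a Cox model has two consequences even in a randomised trial. The treatment hazard ratio is averaged over a more heterogeneous group and lies nearer to 1, and the test in that model loses some power. In addition, if one arm happens to hold more tumour patients, the difference passes into the adjusted hazard ratio. Adding diagnosis after seeing such an imbalance would be post hoc; naming it beforehand avoids that choice. Because the article states the covariate list, this is a fixed choice and not a detail left open for the SAP.

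**Working it through.** **1. The plan's own figures.** Inputs from Sample size considerations: hazard ratio 0.70, type I error 0.05 (taken as two-sided), power 80%, 1:1 allocation, 20% control mortality per year, accrual 1.5 years, duration 3 years, withdrawal 10% per year.

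- Events (Schoenfeld): 4 × (1.960 + 0.842)² / (ln 0.70)² = 247, as stated.
- Patients: with death hazard −ln 0.8, withdrawal hazard −ln 0.9 and uniform accrual, the mean probability of an observed death is 0.3076. 247 / 0.3076 = 803, against the stated 802.

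The planned event number is therefore that of an unadjusted comparison.

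**2. Gain from adding diagnosis.** The documents give no prevalence or hazard ratio for tumour, so both are assumptions shown as a range. The simulated trials had 802 patients, were cut at the 247th death, and had a treatment hazard ratio of 0.70 conditional on the covariates. There were 1,800 runs per row. Only tumour carried a prognostic effect beyond age and Barthel index. The fuller model added the six diagnosis categories and three comorbidities to the planned covariates.

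| Tumour prevalence, mortality HR | Log-rank power | Planned Cox power | Fuller Cox power | Gain (points) | Mean HR, planned → fuller |
|---|---|---|---|---|---|
| 15%, 1.5 | 75.8% | 78.7% | 78.7% | 0.0 | 0.701 → 0.698 |
| 20%, 2 | 74.2% | 77.9% | 78.9% | 1.0 | 0.704 → 0.697 |
| 30%, 2 | 75.6% | 77.6% | 80.1% | 2.5 | 0.698 → 0.690 |
| 20%, 3 | 72.3% | 75.7% | 79.9% | 4.2 | 0.712 → 0.695 |
| 30%, 3 | 71.6% | 73.6% | 78.8% | 5.2 | 0.715 → 0.695 |

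The Monte Carlo standard error of the gain is 0.4 to 0.7 points. The hazard ratio moves by 0.003, 0.007, 0.008, 0.017 and 0.020, that is roughly 0.005 to 0.02 and less in the weakest setting.

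When the other diagnoses and the comorbidities are also given prognostic effects, the gain is 1.1 points (tumour 20%, HR 1.5), 1.6 (20%, HR 2) and 3.0 (25%, HR 2.5). An extreme case outside the assumed range (25%, HR 3.5) gives 7.9.

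**3. If 0.70 is read as the marginal hazard ratio.** In two settings with a stronger conditional effect, chosen so that the unadjusted hazard ratio is about 0.70, power is:

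- log-rank 80.5% and 80.7%;
- planned Cox 82.1% and 83.1%;
- fuller Cox 84.4% and 86.9%.

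The gain is 2.3 and 3.8 points, all above the planned 80%.

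**4. Type I error.** With a true hazard ratio of 1, one-sided rejection was 2% to 3% for every model.

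**5. Chance imbalance.** With 401 patients per arm, prevalence p and tumour hazard ratio H, the standard deviation of the between-arm difference is √(p(1−p) × 2/401). To first order, the shift in the log hazard ratio at the 95% limit is 1.96 × SD × ln H.

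- p = 0.30, H = 2.5: SD = 0.032; shift = 1.96 × 0.032 × 0.916 = 0.058. A true 0.70 reads as 0.66 or 0.74.
- p = 0.15, H = 1.5: SD = 0.025; shift = 1.96 × 0.025 × 0.405 = 0.020. A true 0.70 reads as 0.69 or 0.71.
- p = 0.30, H = 3: shift = 1.96 × 0.032 × 1.099 = 0.070. A true 0.70 reads as 0.65 or 0.75.

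For comparison, the standard error of the log hazard ratio with 247 deaths is about 2/√247 = 0.127. The middle case is 0.058/0.127 = 0.46 of a standard error.

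**The case against.** The strongest reply is that nothing planned is lost. The test named for the primary endpoint is the log-rank test, the 247 events match an unadjusted calculation, and covariates in a Cox model cannot change its power. A reader might infer that the trial gives away power on its primary test; the documents do not support that. If 0.70 is a marginal hazard ratio, the planned Cox model already exceeds 80%. This part of the reply stands and confines the point to the adjusted result.

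Other parts also stand:

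- A reader might infer that the plan contradicts itself by calling diagnosis important and then omitting it. The word is used there of effect modification, and no claim of prognostic strength is made.
- The shift towards 1 might be taken for confounding or bias. It is non-collapsibility: a hazard ratio conditioned on fewer variables, with the type I error intact.
- A chance imbalance is ordinary randomisation variability and is already reflected in the confidence interval.
- The NRS, a covariate and a stratification factor, has a disease-severity part that carries some diagnosis information. The simulation gave no credit for this, so the true gain may be smaller.
- Inflammation status may be incomplete, because blood results depend on routine care. The article states no covariate list for the secondary time-to-event models, so there is nothing to correct there.

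What does not stand is that the choice is immaterial. The Cox model supplies the only mortality effect estimate named with a confidence interval. The NRS is a weak substitute: the eligibility section lists cancer alongside kidney disease, heart failure and COPD under the same severity item, and the score enters as a total mixed with nutritional impairment.

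**Conclusion.** The point holds as an efficiency improvement to the adjusted Cox analysis of mortality. Under the assumed 15% to 30% tumour prevalence and mortality hazard ratio of 1.5 to 3, adding tumour gains about 0 to 5 points of power for that model's test and moves the estimate by roughly 0.005 to 0.02. It also largely removes from the adjusted hazard ratio a shift from chance imbalance that could reach about 0.02 to 0.07 on the log scale at the 95% limit. With weak prognostic effects the gain in power is nil. These sizes rest on values that the documents do not give. The planned covariate set is valid and defensible; it leaves out one plausibly strong predictor that the trial needs to code in any case.

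**What to change.** Before database closure, add main diagnosis at the index stay, at least as tumour yes/no, to the prespecified covariates of the Cox model for mortality. State how tumour is defined. Add a comorbidity only if it is completely recorded at baseline, which should be checked for inflammation status in particular. If the unseen SAP already includes diagnosis, only the article and the SAP need to be aligned.

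Tumour yes/no costs one parameter against 247 deaths; the six diagnosis categories cost five. The binary form also avoids the question of where patients outside the six listed categories belong. No further data are needed beyond what the subgroup analyses already require, and the log-rank test and sample size stay as they are.
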